# TREATMENT OF SUBJECTS

## Investigational product/treatment

### Nerve block procedures

Patients will be randomized into one of three different groups, depending on which regional nerve block type they will receive for pre-operative pain management. The three regional nerve block types are described as follows:

**Femoral Nerve Block**

The femoral nerve block is performed with the patient in the supine position, and guided by ultrasound. The ultrasound transducer is placed transversely on the inguinal crease, and moved in a lateral-to-medial direction to identify the femoral artery. The needle tip is placed immediately adjacent to the lateral aspect of the femoral nerve, below the fascia iliaca, that surrounds the femoral nerve. Negative aspiration should be observed before injection of local anaesthetic into the plane and observation of fluid spread in the desired plane. Then 15 ml of local anaesthetic is injected. Proper deposition of local anaesthetic is confirmed either by observation of the femoral nerve being displaced by the injectate or by the spread of the local anaesthetic above or below the nerve, surrounding and separating it from the fascia iliaca layers. If the spread is deemed inadequate, injection is stopped and the needle is repositioned more laterally or medially to facilitate adequate block placement.

**Fascia Iliaca Compartment Block**

The fascia iliaca nerve block (also called the fascia iliaca compartment nerve block) is performed with the patient in the supine position, and guided by ultrasound. The femoral artery is visualized by placement of the transducer transversely on the inguinal crease. The goal is to place the needle tip under the fascia iliaca approximately at a lateral third of the line connecting the anterior superior iliac spine to the pubic tubercle. Negative aspiration should be observed before injection of local anaesthetic into the plane and observation of fluid spread in the desired plane. The total volume of the injection should be 40 ml. To achieve this, the dose of local anaesthetic (according to the dosing recommendations in Table 1), is topped up to a volume of 40 ml with NaCL. Its spread laterally toward the iliac spine and medially toward the femoral nerve is observed with US visualization. A proper injection will result in the separation of the fascia iliaca by the local anaesthetic in the medial–lateral direction from the point of injection as described. If the spread is deemed inadequate, injection is stopped and the needle is repositioned more laterally or medially to facilitate adequate block placement.

**Pericapsular Nerve Group block**

The PENG block is performed with the patient in the supine position, and guided by ultrasound. The ultrasound probe is initially placed in a transverse plane over the anterior inferior iliac spine, before being aligned with the pubic ramus by rotating the probe 45 degrees counter clockwise. The iliopubic eminence, the iliopsoas muscle tendon, the femoral artery and pectineus muscle should be visualised in this view. The femoral nerve should be identified during scanning prior to needle insertion. The goal is to place the needle tip in the musculofascial plane between the psoas tendon anteriorly and the pubic ramus posteriorly. The total volume of the injection should be 40 ml. To achieve this, the dose of local anaesthetic (according to the dosing recommendations in Table 1), is topped up to a volume of 40 ml with NaCL. Negative aspiration should be observed before injection into the plane and observation of fluid spread in the desired plane. If the spread is deemed inadequate, injection is stopped and the needle is repositioned more laterally or medially to facilitate adequate block placement.

### Medication and dosage

As allocation to the treatment arms will be balanced for each participating centre, participating medical centres should use the NYSORA procedures for ultrasound guided nerve block placement.^31-33^ The type of LA (such as levobupivacaine or ropivacaine) used can be the one of their preference. While doing so, they have to adhere to the dosing recommendations in Table 1. In line with existing guidelines, high-volume low-concentration blocks are advised for FICB and PENG blocks specifically.

|  | **Levobupivacaine** | **Ropivacaine** |
| --- | --- | --- |
| Relative maximal allowed dosage | 2mg/kg | 3mg/kg |
| Absolute maximal allowed dosage | 200mg | 300mg |
| Advised dosage  Weight of 50-60kg  Weight of >60kg | 75mg  100mg | 112,5mg  150mg |

Table 1. Allowed and advised dosages of local anaesthetics.

## Rescue medication (if applicable)

Cooperating medical centres can use their standard, already existing procedures for escape medication by means of opioids. To account for different opioids used in different centers, dose equivalents will be calculated for comparison.

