**Nature and extent of the burden and risks associated with participation, benefit and group relatedness:**

Although PENG, FICB and FNB are overall safe when performed correctly, there are some risks associated with these procedures. These risks include: bleeding (1-2% chance), infection, damage to surrounding structures, (permanent) nerve injury, and intravascular uptake of local anesthetic resulting in systemic toxicity (LAST). In addition, there is a 5-10% chance that the block provides suboptimal analgesia with the need for additional analgesics. Important to note is that PENG, FICB and FNB are all standard care in the ED. However, since all included types of regional anesthesia in the setting of traumatic femur fractures are part of well-established clinical practice, there is no additional risk for the patients participating in this study. **INTRODUCTION AND RATIONALE**

An aging population will result in a growing prevalence of hip fractures.^1,2^ Hip fractures pose an increased risk of mortality, morbidity, and functional impairment.^3^

Adequate perioperative pain reduction is of utmost importance as pain is an important factor influencing complication rates, posing a significant risk for decreased functional outcomes, prolonged time to mobilization and longer hospital stay.^4,5^ Systemic analgesia is commonly used in the pain management of patients with hip fractures, including opioids (e.g. morphine or fentanyl).^6^ However, opioids are associated with adverse events such as delirium, vomiting, pruritus and respiratory depression, which are even more common in older patients.^7,8^ Additionally, opioids are highly addictive, as illustrated by the ongoing worldwide opioid crisis.^9^

An alternative method to obtain adequate analgesia is the use of regional nerve blocks. Nerve blocks have several advantages over systemic analgesia. First, they may provide superior analgesia.^5^ Second, they contribute to a reduction in opioid use and opioid-related adverse events, and thereby decrease the risk of delirium and cognitive dysfunction.^10-12^ Previous research has shown that survival and length of hospital stay are both positively associated with the use of regional anesthesia in hip fractures.^13^ Recent guidelines therefore advise to use regional anaesthetic techniques for pain management in hip fractures.^14-16^

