### Secondary study parameters/endpoints (if applicable)

- - Pre-operative pain scores at 15 min-, 30 min-, and 1 hour post-block placement.
  - The amount of rescue medication calculated as mg/hour given IV in the ED after block placement or SC/IO in the ward during the first 12 hours after block placement or until operation.
  - Number and type of adverse and serious adverse events.

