## Study procedures

Before the start of the data collection, a refamiliarization session for all three nerve block procedures will be hosted in each individual center. In this refamiliarization session, an expert in POCUS will provide theoretical and practical training in block placement for each of the three blocks, and will test and log the skill level of the participating physicians in a dedicated training log. Only physicians who are able to perform all three blocks in line with the NYSORA guidelines are eligible for participation in the study.^31-33^

[figure not shown]

**Figure 2**. Timeline of the study procedure, showing which data will be collected at what time point.

Data will be gathered at 6 different time points (T1-T6). *Figure 2* shows a detailed timeline of data collection.

Pre-block characteristics (demographic data (age, sex, weight), ASA score, pain scores (VAS) during rest and light elevation of the affected leg, type of fracture, analgesics administered before hospital admission (including medication routinely used by the patient), block characteristics (type of block, visualization of landmarks, amount- and type of LA administered, timing of block placement), and post-block characteristics (total amount of opioids administered in the first 12 hours after block administration and (S)AE’s) will be reported in an electronic case report form (appendix IV).

The primary endpoint, quality of recovery, will be measured either 6-8 hours post-block, or pre-OR (whichever one comes first) with the Quality of recovery-15 (QoR) patient-reported outcome questionnaire that measures the quality of recovery after surgery and anaesthesia.^34^ To ensure patients will be adequately rested for their operation, QoR-15 registration will be postponed until the next morning for blocks placed between 17.00 and 22.00 hours, as QoR-15 registration would then fall between 23.00 and 6.00. The QoR-15 questionnaire can be found in the appendices (*Appendix III*). Previous studies have shown a good convergent validity between the QoR-15 and the visual analog scale (VAS). Additionally, validity of the QoR-15 is supported by a negative correlation with duration of surgery and duration of hospital stay, and the QoR-15 shows excellent internal consistency, split-half reliability, test–retest reliability, and responsiveness.^34^

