***Zie volgende pagina!***

**Data te verzamelen 12 uur na block procedure**

Opioïden toegediend na block (incl. dosering)

..…..…………………………………………………..…..…………………………………………….

..…..…………………………………………………..…..…………………………………………….

..…..…………………………………………………..…..…………………………………………….

Tijdstip meting opioïden: .... : .… uur *(zoals 9:30, op het moment dat het half 10 in de ochtend is)*.

Hoeveelheid benodigde opioïden: ……. mg/uur

(S)AE’s voorgekomen (omcirkel) : Ja / Nee

Indien “Ja”, specificeer : …..…………………………………………………

..…..…………………………………………………..…..…………………………………………….

..…..…………………………………………………..…..…………………………………………….

Is er sprake van een verband tussen LA en SAE? (omcirkel) Ja / Nee

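### The rescue endpoint is defined by purpose and route, but the plan records all post-block opioids without either, and no other post-block analgesia

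*Protocol*

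**What the plan says.** Protocol sections 1 and 5.1.2 name the secondary endpoint: "The amount of rescue medication calculated as mg/hour", restricted to doses "given IV in the ED after block placement or SC/IO in the ward", over 12 hours or up to surgery. Section 4.2 says that centres may use their "standard, already existing procedures for escape medication by means of opioids" and that, because opioids differ between centres, "dose equivalents will be calculated for comparison".

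Section 5.3 describes what is collected after the block: "total amount of opioids administered in the first 12 hours after block administration", together with adverse events. Appendix IV has one free-text item, "Opioïden toegediend na block (incl. dosering" (opioids given after the block, with dose), the time of that reading, and a derived mg/hour figure. Neither place asks for the route or the reason for a dose.

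Before the block, section 5.3 records analgesics, "including medication routinely used by the patient". No rule links this baseline item to the post-block total.

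The Summary, under burden and risks, gives a 5-10% chance that "the block provides suboptimal analgesia with the need for additional analgesics". The post-block items in section 5.3 and Appendix IV include no analgesic other than opioids.

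**The concern.** The endpoint has a purpose (rescue) and named routes; the data item has neither. The two can diverge in both directions.

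Upwards, a patient who takes an opioid at home and continues it in hospital adds to the recorded mg/hour although the dose says nothing about the block. Downwards, a patient whose poor block is treated only with something other than an opioid adds nothing.

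The first mainly adds variance. The second could distort the comparison between arms, because the trial is non-blinded (section 2) and the choice of rescue follows local procedure. Opioid use is one of the quantities the Introduction says the trial will assess. The reason for a dose may also be hard to establish after the event, so an analysis plan written later cannot be counted on to repair it.

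**Working it through.** **1. The plan's own figure.** The only planning figure is for QoR-15. With a difference of 6, SD 10, two-sided 0.05 and power 0.9, n per arm = 2 × (1.960 + 1.282)² × 10² / 6² = 58.4, so 59; the t-test version gives 59.35, so 60. Then 3 × 60 = 180 and 180 × 1.10 = 198, as stated. No figure is given for the rescue endpoint, and this point does not depend on the sample size.

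**2. Definition and collection side by side.**

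| Element | Sections 1, 4.2 and 5.1.2 | Section 5.3 and Appendix IV |
| --- | --- | --- |
| Drug | Opioid used as rescue | Any opioid |
| Route | IV in the ED; SC or IO on the ward | Not asked |
| Purpose | Rescue | Not asked |
| Other post-block analgesia | Not covered | No item |

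**3. Four cases traced through both.**

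- Opioid given IV in the ED for fracture pain: in the definition and in the record.
- Regular home opioid continued by mouth or patch: outside the definition by route, but in the record.
- Regular opioid given by a listed route: not rescue by meaning, but in the record. Knowing the route alone would not remove it.
- Poor block treated without any opioid: 0 mg/hour, with no item that shows the treatment.

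**4. How many patients the last case could involve.** 198 / 3 = 66 per arm. 0.05 × 66 = 3.3 and 0.10 × 66 = 6.6, so about 3-7 per arm (3-6 per arm of 60). This is an upper limit: it would be reached only if none of these patients received an opioid. The documents do not say what share would.

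**5. Noise from regular opioids, as illustration only.** None of these inputs is in the documents. Assume a rescue SD of 0.7 mg/hour, a share p = 10% of patients on regular opioids, and an added amount a = 2.5 mg/hour in oral equivalents. Variance with regular users = SD² + p(1 − p)a².

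- 0.49 + 0.09 × 6.25 = 1.05. SD ratio = √(1.0525 / 0.49) = 1.47. Effective n = 60 × 0.49 / 1.0525 ≈ 28.
- If the SD is on a parenteral scale and the oral-to-parenteral ratio is assumed to be 2, a = 1.25: 0.49 + 0.09 × 1.5625 = 0.631, SD ratio 1.13, effective n ≈ 47.
- If that ratio is 3, a = 0.83: 0.49 + 0.09 × 0.694 = 0.553, SD ratio 1.06, effective n ≈ 53.
- Over an SD of 0.5-1.0, a share of 5-15% and an added 1.25-2.5 mg/hour without conversion, the SD ratio runs from 1.04 to 2.05.

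The result moves from negligible to large with the assumptions, so it gives no usable estimate.

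**The case against.** Several objections have force.

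- **No endpoint classifies block failure.** A reader might infer that home opioids are counted as failed blocks. The measure is an amount, so they can only inflate it. As defined, oral and patch doses do not count at all; they enter through the wider collection wording. This stands, and it places the defect in the mismatch between definition and collection.
- **Rescue by other means is hardly mentioned.** Section 4.2 speaks of opioids. The Summary's phrase on further analgesics is general and compatible with opioids, and a repeat block appears nowhere. A reader might infer that failed blocks will routinely score zero; the documents do not support that. What stands is that, if it happens, the listed items would not show it.
- **Other data give some trace.** Home analgesics are recorded at baseline, pain is scored at 15, 30 and 60 minutes, and section 8.1 seeks access to the relevant journal entries. This helps in part. The baseline list does not show which doses were given in the 12 hours, pain scores stop at one hour, and a chart may give route and time without the reason.
- **Appendix IV is incomplete evidence.** It stands in for an electronic form, and some items listed in section 5.3, such as block type, do not appear in its text as available here. The point therefore rests mainly on section 5.3, whose post-block list is opioids and adverse events.
- **Randomisation within centre balances home opioid use on average, and adjustment can be left to the SAP.** Both are true. An SAP can adjust only with what has been recorded.

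**Conclusion.** The recorded mg/hour is not the endpoint that sections 1 and 5.1.2 name, because route and reason are not collected. Regular opioids enter it and cannot be reliably taken out. The main consequence is noise in a secondary endpoint, of unknown size. The illustrative loss from 60 to about 28 patients' worth of information should not be read as an estimate: every input is assumed, it falls to about 47-53 with a parenteral conversion, and section 7 foresees non-parametric analysis of non-normal data, for which a variance formula is only a rough guide.

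The second part is conditional. At most about 3-7 patients per arm of 66 could have a poor block and yet count as 0 mg/hour, and then only if they receive no opioid. It becomes bias only if the choice of rescue differs between arms, which the non-blinded design permits but the documents do not show.

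Severity is minor. The primary QoR-15 comparison and its sample size are not put in question by this point.

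**What to change.** - Make sections 1, 5.1.2, 5.3 and the eCRF describe the same quantity, including whether the route limits are meant to stay.
- For each post-block opioid dose, record drug, dose, route, time, and whether it continues regular home medication or was given for fracture pain after the block.
- Exclude continued home opioid from the rescue total, and report total opioid as a sensitivity analysis.
- Add one eCRF line for any other analgesic or further block after the study block, with time, and report it as a supporting yes/no measure.

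The endpoint should not be narrowed to on-demand doses. Section 4.2 allows local procedures, and a centre may schedule rescue after a poor block; such doses would then be lost, and the result would depend on how each centre charts.

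The cost is a few eCRF fields filled from the medication chart, slightly more data entry, and one revised endpoint sentence. Care is unchanged.

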# METHODS

## Study parameters/endpoints

### Main study parameter/endpoint

Score on the QoR-15 questionnaire.

### Secondary study parameters/endpoints (if applicable)

- - Pre-operative pain scores at 15 min-, 30 min-, and 1 hour post-block placement.
  - The amount of rescue medication calculated as mg/hour given IV in the ED after block placement or SC/IO in the ward during the first 12 hours after block placement or until operation.
  - Number and type of adverse and serious adverse events.

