## Sample size calculation

Sample size was based on the primary outcome measure (QoR-15 score) and a superiority design. Following this design, an independent samples t-test was used, reasoning that one block would be superior to all others if it outperforms its best performing competitor. Based on previous research, a clinically relevant difference is determined at 6.0 points difference in QoR-15 scores.^27^ Also based on previous literature, a standard deviation of 10 is used.^28-30^ A power of 0.9 is used to minimize the chance of missing differences between the groups, as the differences in scores are likely to be small. In order to detect this difference between any of the three groups with a pre-defined p-value of 0.05, 180 patients are needed (distributed over three groups of 60). To account for 10% attrition, i.e. potential dropouts during the study process, a total of 198 patients will be included.

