# STATISTICAL ANALYSIS

Standard descriptive statistics will be used to summarize patient characteristics. Continuous data will be inspected for normality before analysis (Shapiro-Wilk), summarized with mean and standard deviation if normally distributed, or median and 25-75th centiles (Q1, Q3) if not normally distributed, and evaluated for differences with the One-Way ANOVA (if normally distributed) or Friedman Test (if not normally distributed). Categorical data will be summarized by frequency count and percentage calculations. Examination of possible associations between data will be done by Chi-Square Test or Logistic Regression. LA-type will be used as an interaction term to investigate the influence of the type of LA used. If needed, quantile regression, suitable for skewed data, will be used to identify confounders that may impact on postoperative quality of recovery scores. A two-tailed P-value <0.05 will be taken to indicate statistical significance.

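### Rescue opioid use is defined only as a per-patient mg/hour, and if few patients need rescue the planned median and quartiles would read 0 (0-0) in every arm

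*Protocol*

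**What the plan says.** The secondary objectives (section 1) and section 5.1.2 give rescue use one metric: "The amount of rescue medication calculated as mg/hour given IV in the ED after block placement", then on the ward, with the window closing at 12 hours or at surgery if that is earlier. The case report form (Appendix IV) has one mg/hour field per patient, beside the list of opioids given and the time of the opioid measurement.

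Section 7 handles all continuous data alike. After a Shapiro-Wilk check they are summarised by mean and SD, or by "median and 25-75th centiles (Q1, Q3) if not normally distributed". They are then "evaluated for differences with the One-Way ANOVA (if normally distributed) or Friedman Test (if not normally distributed").

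The only figure on need for extra analgesia is in the risk paragraph of the Summary: "there is a 5-10% chance that the block provides suboptimal analgesia with the need for additional analgesics". Section 3.4 plans 60 patients per arm for the primary endpoint and makes no calculation for rescue use.

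**The concern.** Opioid use is one of the three outcomes named in the study aim, with pain and patient-reported outcome. A per-patient rate is exactly zero for everyone who needs no rescue. If most patients need none, the median and both quartiles are zero in every arm, and the planned summary cannot separate an arm with few users from one with twice as many.

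The denominator is a second, smaller matter. Each patient's hours stop at operation, so theatre timing changes the score that a given dose receives.

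**Working it through.** **Inputs from the protocol.** 60 per arm and 198 enrolled (66 per arm) in section 3.4; the mg/hour definition in 5.1.2; the median and quartile branch in section 7; 5-10% in the Summary. The documents give no rescue rate, dose distribution or time to surgery, so these are varied or labelled as assumed.

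**The plan's own figure.** For 6 points, SD 10, two-sided 0.05 and power 0.9: n = 2 × (1.960 + 1.282)² × 10² / 6² ≈ 58.4, so 59 per arm. The t-test version gives 59.35, so 60 per arm and 180 in total; 180 × 1.1 = 198. The stated size is reproduced, and n = 60 is used below.

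**When the upper quartile leaves zero.** Under five common quartile definitions, Q3 exceeds 0 with n = 60 only if at least 15 patients (four definitions) or 16 (one definition) receive any opioid. With n = 66 the threshold is 16 or 17. Let X ~ Binomial(60, p) be the users in an arm and r the threshold. Then P(all three arms read 0 (0-0)) = [1 − P(X ≥ r)]³.

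| Use p | Expected users of 60 | P(Q3 > 0), one arm | P(all three arms 0 (0-0)) |
|---|---|---|---|
| 5% | 3 | below 0.000001 | about 1 |
| 10% | 6 | 0.0002-0.0007 | 0.998-0.999 |
| 15% | 9 | 0.014-0.029 | 0.92-0.96 |
| 20% | 12 | 0.13-0.21 | 0.50-0.66 |
| 25% | 15 | 0.43-0.55 | 0.09-0.18 |
| 30% | 18 | 0.76-0.84 | 0.004-0.015 |

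With 66 per arm the pattern is the same: at least 0.998 at 10%, 0.91-0.95 at 15% and 0.45-0.60 at 20%.

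**The median.** It exceeds 0 only with at least 30 users of 60. At 30% use the chance is 0.00091 per arm, so all three medians are zero with probability (1 − 0.00091)³ = 0.997. At 40% use it is (1 − 0.0746)³ = 0.79.

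**Use doubled in one arm (10/10/20%).** P(all Q3 = 0) = (1 − 0.000666)² × (1 − 0.2065) = 0.79 at threshold 15, and (1 − 0.000201)² × (1 − 0.1306) = 0.87 at threshold 16.

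**The denominator.** Take one 5 mg dose, assumed for arithmetic only. Over 2 h it scores 5/2 = 2.5 mg/h, over 4 h 1.25, and over 12 h 0.42, so the 2-hour window gives six times the 12-hour score. Suppose a fraction f of patients have window t and the rest 12 h, and the chance of one dose does not depend on the window. The early patients' share of the mean is then (f/t) / (f/t + (1 − f)/12). For f = 0.1 and t = 2 this is 0.05 / (0.05 + 0.075) = 40%; for f = 0.2 and t = 4 it is 0.05 / (0.05 + 0.0667) = 43%. If dosing is proportional to time at risk, the share is f itself, 10% or 20%.

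**What a proportion could show with 60 per arm.** Two-sided 0.05, normal approximation. For 5% against 10%, (0.05 − 1.96 × 0.0481) / 0.0479 = −0.92, so power is about 18%. For 10% against 30%, (0.20 − 1.96 × 0.0730) / 0.0707 = 0.80, so power is about 79%.

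**The case against.** The strongest reply is that 5-10% is not a rescue forecast. It describes block failure in a paragraph about patient risk and enters no design calculation. Other text leaves room for more use: the Introduction says that FNB and FICB are not always adequate, section 6.2.3 says that the local anaesthetic works for 8-12 hours and so may wear off inside the window, and section 4.2 leaves rescue to local procedures. This stands. A reader might infer that every arm will read 0 (0-0); the documents support that only conditionally, and the pattern is gone by about 30% use. The zero medians last longer.

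A reader might also infer that patients operated early dominate any mean. The documents do not support this. It needs assumed surgery times and dosing unrelated to time at risk, and a mean is not the planned summary for skewed data. Dividing by hours is an ordinary adjustment for unequal windows.

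Third, a 0 (0-0) summary does not empty the comparison, because a rank test still uses the non-zero values. In a simulation of 10/10/30% users (60 per arm; assumed 30% operated at 2-6 h and one or two 5 mg doses), power was 84% for Kruskal-Wallis on mg/hour, 85% for chi-square on any use and 62% for ANOVA. ANOVA is reserved for normal data, so its lower figure is no argument here. The proportion therefore gains an interpretable effect, not power over a rank test. But section 7 names no rank test for independent groups: the Friedman test is for related samples, and these are three separate arms.

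Last, handling of zeros might be left to a statistical analysis plan. That would answer a silence, but here the protocol itself fixes both the metric and its summary.

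**Conclusion.** The point holds conditionally. If rescue use is near 5-10%, the planned summary would almost surely be 0 (0-0) in all three arms (probability at least 0.998). At 15% use it very probably would be, at 20% it is about even or somewhat better, and by 30% it would not. All medians stay at zero to about 30% use and beyond. In the low range, a doubling in one arm would usually not show in the summary.

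This rests on 60 analysed patients per arm, independent patients, and zero-heavy data failing the normality check, which is close to certain. The effect of the variable window on a mean cannot be sized from the documents. Nor do they support discarding per-patient rates for a ratio of arm totals, which is a trade-off rather than a correction. Because the endpoint is secondary, the severity is modest.

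**What to change.** In sections 5.1.2 and 7:

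- Add the number and percentage of patients given any rescue opioid before operation or 12 hours, whichever is earlier, with pairwise risk differences and 95% CIs. Report it ahead of the amount.
- Keep mg/hour in dose equivalents as the supporting amount. Report it also among users only, with total dose and total hours observed per arm, so that a reader can see whether the windows differ.
- Compare mg/hour across arms with a test for independent groups, for example Kruskal-Wallis.

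The cost is wording and one more secondary summary, with no new patients or visits. The form already records the opioids given, the block time and the time of the opioid measurement; operation time, where it closes the window, is already needed for mg/hour. Precision is modest: about 18% power for 5% against 10%, and about 79% for 10% against 30%. The intervals should therefore be read as estimates, not as proof of no difference. The proportion also depends on how long each patient is observed, which is why the hours per arm belong beside it.

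### The rescue-opioid endpoint is limited by route and ends at operation, but data collection takes a 12-hour total of all opioids, and the form as shown cannot turn one into the other

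*Protocol*

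**What the plan says.** Section 5.1.2 lists as a secondary endpoint "The amount of rescue medication calculated as mg/hour", and it restricts the count to opioids "given IV in the ED after block placement or SC/IO in the ward during the first 12 hours after block placement or until operation". The secondary objective in Section 1 gives the same routes and the same window.

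Section 5.3 describes what goes into the electronic case report form, and there the item is the "total amount of opioids administered in the first 12 hours after block administration". It names no route and does not stop at operation.

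Appendix IV follows Section 5.3. The block of items is headed "Data te verzamelen 12 uur na block procedure" (data to collect 12 hours after the block). It holds a free-text entry, "Opioïden toegediend na block (incl. dosering" (opioids given after the block, with dose), one time of opioid measurement and one mg/hour figure.

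Section 4.2 lets each centre keep its existing opioid procedure for rescue and says that "dose equivalents will be calculated for comparison".

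**The concern.** The endpoint and the data meant to supply it cover different doses over different periods.

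- **Route.** Section 4.2 does not fix the route of rescue, so a centre may give opioids by a route or in a place that Section 5.1.2 does not list. IV on the ward is one example, and a non-IV dose in the ED is another. Such doses fall outside the endpoint but inside the collected total.
- **Window.** Section 5.3 schedules the QoR-15 at 6 to 8 hours or before the OR, whichever is earlier, so the plan expects some patients to reach surgery well inside 12 hours. For them a 12-hour total can take in anaesthetic and postoperative opioids, which do not measure how well the ED block worked before surgery.

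Opioid use is part of the study aim given in the introduction. Section 2 describes the trial as non-blinded. Two usable definitions of one outcome then leave room to choose between them after the data have been seen.

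**Working it through.** The protocol states no figure for this endpoint, so there is none to reproduce. The check sets the texts side by side and then asks how far the two rates can differ.

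**Texts compared**

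| Element | Sections 1 and 5.1.2 | Section 5.3 and Appendix IV |
| --- | --- | --- |
| Routes and places | IV in the ED; SC/IO on the ward | All opioids, no route named |
| End of window | 12 hours or operation | 12 hours |
| Time of operation | Needed for the window and the hours | Not listed in 5.3; no field on the form as shown |
| Route and time of each dose | Needed to select the doses | No field on the form as shown |
| Elapsed hours | Needed for mg/hour | Block time and one opioid measurement time |

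The endpoint does not say which of 12 hours and operation applies. The earlier of the two is the natural reading and is used here.

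**Formulas**

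- Endpoint wording, operation at t hours with t below 12: rate = A / t, where A is the dose by listed routes before operation.
- 12-hour total: rate = (A + U + P) / 12, where U is the preoperative dose by unlisted routes and P is the dose given during and after surgery up to hour 12. The divisor of 12 assumes that the measurement time is 12 hours, as the form's heading implies.

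**Assumed values** (not in the protocol, in mg equivalents): A = 10, P = 0 to 20, U = 0 or 5, t = 4 to 10 hours.

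**Effect of the window (U = 0)**

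| t (h) | Endpoint, 10 / t | Total, P = 0 | Total, P = 10 | Total, P = 20 |
| --- | --- | --- | --- | --- |
| 4 | 2.50 | 0.83 | 1.67 | 2.50 |
| 6 | 1.67 | 0.83 | 1.67 | 2.50 |
| 8 | 1.25 | 0.83 | 1.67 | 2.50 |
| 10 | 1.00 | 0.83 | 1.67 | 2.50 |

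The totals are 10/12, 20/12 and 30/12. Setting A / t = (A + P) / 12 shows that the two rates agree only when P = A × (12/t − 1). With A = 10 and t = 8 that is 10 × 0.5 = 5 mg. With a smaller P the 12-hour total gives the lower rate, and with a larger P the higher one. At t = 8 the ratio of total to endpoint runs from 0.83/1.25 = 0.67 to 2.50/1.25 = 2.0.

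**Effect of the route (t = 8, U = 5)**

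The endpoint wording gives 10/8 = 1.25 mg/h. All preoperative opioids give 15/8 = 1.88 mg/h.

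**The case against.** The strongest reply is that there is only one definition. Sections 1 and 5.1.2 agree word for word on routes and window, and Section 5.3 merely lists what is recorded. A trial may collect a broad total and derive a narrower endpoint, with the derivation left to a statistical analysis plan that is not shown. That would answer the point if the collected items allowed the derivation. Neither the list in Section 5.3 nor the form as shown has the time of operation, or the route and time of each dose, so the narrower quantity cannot be derived from them.

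A second reply is that the form as shown is incomplete. Section 5.3 says that block type, landmark visualisation and pre-block pain scores are recorded, yet the form shows none of them. The real form will be electronic, Figure 2 was not available for this review, and Section 8.1 seeks access to the patient record, which may hold operation and drug times. This is fair, and the absence of a field cannot be taken as proven for the final form. It does not remove the difference in wording between Sections 5.1.2 and 5.3.

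Some stronger readings are tempting and are not supported:

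- **The hours behind mg/hour cannot be verified at all.** Block time and opioid measurement time give the hours up to that measurement. What is missing is any instruction that the measurement stops at operation.
- **The mg/hour field conflicts with dose equivalents.** It does not. The form records opioids with dose, and Section 4.2 makes conversion a later calculation.
- **Oral rescue scores zero.** This depends on what IO means, and the list of abbreviations does not define it. IV on the ward is unlisted on either reading.

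**Conclusion.** The inconsistency is real and should be repaired, but it is a matter of measurement in one secondary endpoint. As written, the endpoint omits doses by unlisted routes, and the collected total can include surgical opioids.

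Its size cannot be fixed from the protocol, which gives no opioid doses and no distribution of time to surgery. With the assumed doses the 12-hour total ranges from two thirds to twice the endpoint rate for a patient operated on at 8 hours. A reader might infer that early surgery always inflates recorded use. The arithmetic shows that it can lower it as well.

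A reader might also infer that the comparison between blocks is biased. The protocol does not support that. Section 5.2 randomises in blocks, 1:1:1, within every centre, so local route policy is balanced across arms by design, and factors fixed before randomisation that drive time to surgery are balanced in expectation. The likely harm is added noise, dilution of any opioid-sparing difference, and a definition that could be chosen after the results are known. The QoR-15 primary endpoint and the sample size built on it are untouched.

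The conclusion assumes that some patients reach the OR within 12 hours, which the plan foresees, and that at least some rescue is given by an unlisted route, which Section 4.2 allows but no section confirms.

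**What to change.** Put one measurement definition in Sections 1, 5.1.2 and 5.3 and in Appendix IV: all rescue opioids by any route, converted to the dose equivalents already planned in Section 4.2, from block placement to the earlier of OR entry or 12 hours, divided by the hours observed. Counting every route widens the endpoint as now worded. If the sponsor prefers to keep a route list, the same list should appear in all four places. Either way, define or correct IO.

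Add to the form the time of OR entry and, taken from the medication record, the route and time of each dose alongside the drug and dose. The mg/hour figure can then be calculated from these entries in the same way for every centre.

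The cost is a wording change in four places and a few more data fields per patient. It alters only what is counted and recorded; rescue treatment itself stays as each centre gives it.
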